## Abstract

**Introduction:**

Family-based physical activity (PA) interventions present a promising avenue to promote children’s activity; however, high-quality experimental research is lacking. This paper describes the protocol for the FRESH (Families Reporting Every Step to Health) pilot trial, a child-led family-based PA intervention delivered online.

**Methods and analysis:**

FRESH is a three-armed, parallel-group, randomised controlled pilot trial using a 1:1:1 allocation ratio with follow-up assessments at 8 and 52 weeks postbaseline. Families will be eligible if a minimum of one child in school Years 3–6 (aged 7–11 years) and at least one adult responsible for that child are willing to participate. Family members can take part in the intervention irrespective of their participation in the accompanying evaluation and vice versa.

Following baseline assessment, families will be randomly allocated to one of three arms: (1) FRESH; (2) pedometer-only or (3) no-intervention control. All family members in the pedometer-only and FRESH arms receive pedometers and generic PA promotion information. FRESH families additionally receive access to the intervention website; allowing participants to select step challenges to ‘travel’ to target cities around the world, log steps and track progress as they virtually globetrot. Control families will receive no treatment. All family members will be eligible to participate in the evaluation with two follow-ups (8 and 52 weeks). Physical (eg, fitness and blood pressure), psychosocial (eg, social support) and behavioural (eg, objectively measured family PA) measures will be collected at each time point. At 8-week follow-up, a mixed methods process evaluation will be conducted (questionnaires and family focus groups) assessing acceptability of the intervention and evaluation. FRESH families’ website engagement will also be explored.

**Ethics and dissemination:**

This study received ethical approval from the Ethics Committee for the School of the Humanities and Social Sciences at the University of Cambridge. Findings will be disseminated via peer-reviewed publications, conferences and to participating families.

**Trial registration number:**

ISRCTN12789422

Strengths and limitations of this studyThis pilot trial is among the first physical activity (PA) interventions that specifically targets and evaluates whole family engagement.Novel methodological work will be completed to compute family co-participation in PA using objective measures.The use of mixed methods will provide unique insight and context for our quantitative findings.A long-term follow-up (52 weeks postbaseline) will enable assessment of the potential for long-term effects and an accurate assessment of long-term participant retention, which is notoriously challenging in child-based research.However, this pilot trial will not allow us to draw conclusions of effectiveness.

## Introduction

Although the benefits of regular physical activity (PA) in children are well-established,^1 2^ roughly only half of UK children meet the recommended 60 min of daily moderate-to-vigorous intensity PA (MVPA).^3^ Moreover, observational data reveal that children are less active after school and at weekends compared with during school time, that children in rural areas are less active than their urban counterparts, and that MVPA declines steeply as children enter adolescence, particularly at weekends.^4–7^ Intervening prior to adolescence may be important to help young people to reach or maintain adequate PA levels.

Targeting families may, therefore, be one avenue to increase PA among children.^8 9^ In particular, parents can influence their children’s health behaviours through a variety of mechanisms, including their general parenting style, parenting practices (eg, rule setting, behavioural consequences and establishing behavioural expectations) and their control over the home environment.^10 11^ Parents can also act as gatekeepers to activity^12^ and can play an important role in increasing their child’s PA through role modelling or parental support.^13^ However, little PA promotion research has been conducted in the family compared with the school setting.^14 15^ Previous research suggests that: (1) involving family members is critical for sustained behaviour change^13 16 17^ and (2) home-based PA interventions that include the family are potentially more effective than those requiring the family to travel to community or other intervention locations.^18 19^ Many studies, however, only focus on promoting child PA instead of considering the family as a unit that may work together to change behaviour.^20^

Our recent feasibility study^21^ was among the first PA interventions to specifically target whole family engagement. The findings showed that it was feasible and acceptable to deliver and evaluate a family-targeted PA promotion intervention with high acceptability from participating families. Building on this work, this paper describes the protocol for the Families Reporting Every Step to Health (FRESH) pilot trial. The aims of this pilot study are to: assess the feasibility and acceptability of the revised recruitment strategy, intervention and outcome evaluation (after feasibility testing^21^); study long-term retention; and explore further intervention optimisation and preliminary effectiveness.

## Methods and analysis

The Standard Protocol Items: Recommendations for Interventional Trials^22^ is used to guide the reporting of this study. We also use the Template for Intervention Description and Replication^23^ to guide our description of the intervention.

### Trial design

FRESH is a three-armed, parallel-group, randomised controlled pilot trial using a 1:1:1 allocation ratio with follow-up assessments at 8 and 52 weeks postbaseline (see figure 1). Following baseline assessment, families will be randomly allocated to one of three arms: (1) FRESH arm; (2) pedometer-only arm or (3) no-intervention control arm. All family members in the pedometer-only and FRESH arms receive pedometers and generic family PA promotion information. FRESH families additionally receive access to the intervention website. Control families will be asked to carry on as normal.

**Figure 1 F1:**
[figure not shown]
Participant flow diagram. FRESH, Families Reporting Every Step to Health.

### Participants

Families are deemed eligible to participate in this study if there is consent from at least one child in school Years 3–6 (aged 7–11 years, hereafter referred to as the index child) and at least one adult responsible for the index child. The adult must live with the index child in the main household (ie, the index child’s primary residence as indicated by the parent). There are no restrictions placed on family type (eg, single parent, shared parenting and inclusion of extended family living in the main household) and no maximum number of participants per family. All participants need to be able to perform light-intensity PA (eg, walking), have access to the Internet and understand the English language sufficiently well to provide informed consent. Family members are able to take part in the intervention irrespective of their participation in the accompanying evaluation and vice versa. Exclusion criteria related to participation in specific assessments are outlined below with the outcome measures.

### Setting

Families will be recruited from rural Norfolk and Suffolk, counties in East Anglia, UK. Norfolk is 2074 square miles in size and had a total estimated population of 898 400 in 2017 (most recent estimate)^24^ and Suffolk is 1466 square miles and had a total estimated population of 756 978 in 2017 (most recent estimate).^25^ According to the Norfolk and Suffolk county councils,^26 27^ approximately 53% and 42% of the Norfolk and Suffolk populations, respectively, are classified as living in a rural area. Based on the Office for National Statistics^28^ classification, ‘rural’ will be defined as having a postcode falling in a small town, village, hamlet or dispersed settlement. In both counties, existing inequalities have been identified, including PA, obesity and other indicators of child ill health, school readiness and attainment.^6 29 30^

### Recruitment

The recruitment of families is known to be particularly challenging^11 13^ and we have described specific recruitment challenges we have encountered previously.^21^ To overcome these challenges, we will use a multifaceted recruitment strategy, including targeting adults (parents) directly and messaging, which focuses on the wider benefits of research participation (eg, spending more time together as a family) as opposed to solely focusing on increasing PA or obesity prevention.^31^ Recruitment will be undertaken over an estimated 3 months (with a recruitment rate of ~20 families/month), using two main strategies that target adults and children, as summarised in figure 2. The first strategy involves recruitment in the school setting and the second in employer-based and community-based settings (eg, Brownies/Cubs, community centres and general practitioner surgeries). Alternative recruitment settings may also be explored (eg, online/traditional media) if needed, and will follow the same procedure as the second strategy. For logistical purposes, we aim to find recruitment settings located roughly within an hour commute of Cambridge, UK.

**Figure 2 F2:**
[figure not shown]
Recruitment strategy. FRESH, Families Reporting Every Step to Health.

#### Recruitment protocol

To recruit schools, employers and community-based organisations, we will aim to first contact those in lead positions (eg, head teachers, human resources, health and well-being leaders, and heads of community-based organisations). An information pack detailing the purpose of the study and all procedures will be included in our correspondence with lead personnel. Also included in the information pack and recruitment material will be a link to a recruitment video, which was developed with families following the suggestion of participants in the FRESH feasibility study.^21^ For school-based recruitment, verbal or written approval will be sought to send home study leaflets with children, circulate our leaflet to parents online and send an online reminder to parents approximately 2 weeks later. We will also seek permission to present to Key Stage 2 students (Years 3–6; aged 7–11 years) at a scheduled school assembly. Similarly, for employer-based and community-based recruitment, we will seek approval to circulate our study information to employees or members either online or hardcopy. In all cases, interested parents are asked to express interest by contacting the study team via email or a free-to-call telephone number, after which eligibility will be assessed and study information emailed. A baseline assessment appointment will be made with families still interested in participating. Written informed consent will be obtained for all participating adults and written parental consent and child assent for each participating child during this appointment, prior to baseline assessments.

#### Retention

To encourage retention, we will remain in regular contact with all participating families (through intervention website and newsletter/holiday cards), and offer measurement incentives and study feedback. Each individual participant will receive a £5 voucher on return of the accelerometer and global positioning system (GPS) monitors at each measurement time point. Retention will be monitored by study group and demographic characteristics to observe whether differences in retention occur.

### Randomisation

Randomisation will occur after baseline assessments and the unit of randomisation will be at the family level (ie, the index child and all participating family members). Families will be randomised in blocks of six by an independent statistician using a computer-generated algorithm produced with Stata V.14 and stratified by county (ie, Norfolk or Suffolk). The random allocation sequence will be implemented via a database created in-house on Microsoft Access by independent data management staff. A study coordinator will use the database after baseline to determine which study arm a family is allocated to. No one directly involved in the evaluation will have access to the allocation code or complete sequence.

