### Blinding

Researchers conducting analyses will be blinded to family treatment allocation. Research assistants will not be explicitly told family treatment allocation. However, it will not be possible to conceal treatment allocation from participating families.

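### One fixed block size of six within county leaves at most 20% of allocations predictable to someone who has seen every earlier one; undisclosed varying blocks would cheaply reduce this

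*Protocol article*

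**What the plan says.** Trial design describes a "three-armed, parallel-group, randomised controlled pilot trial using a 1:1:1 allocation ratio". Under Randomisation, "the unit of randomisation will be at the family level", and the list is built as follows: "Families will be randomised in blocks of six by an independent statistician using a computer-generated algorithm produced with Stata V.14 and stratified by county". The strata are Norfolk and Suffolk. Only one block size is given, and nothing says that it is withheld from anyone.

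The same section sets out safeguards. An independent statistician generates the list, independent data management staff build the database, allocation follows baseline, and people directly involved in the evaluation cannot see the code or the full sequence. Individual allocations do become visible one at a time: "A study coordinator will use the database after baseline to determine which study arm a family is allocated to". Under Blinding, analysts are masked and research assistants are not explicitly told the arm, but for families: "However, it will not be possible to conceal treatment allocation from participating families".

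Recruitment protocol has interested parents contact the study team, after which eligibility is checked and a baseline appointment is made. It does not say whether the coordinator is part of that work.

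**The concern.** Withholding the list does not prevent counting. When the block size is constant and known, the allocations already made in the open block determine what remains in it. An observer who has followed a county's allocations knows the last assignment of every block, sometimes the fifth as well, and can often rule out an arm earlier.

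Randomising after baseline stops a family's revealed arm from affecting its own baseline data. It does not stop an expected arm from affecting which interested family is booked next, or how hard it is pursued. What is at stake is the comparability of the arms in the activity contrasts, and the adherence criterion in the Discussion (more than 75% of FRESH families uploading steps at least six times in the first 3 months). With 60 / 3 = 20 families per arm, each FRESH family counts for 1/20 = 5 percentage points of adherence.

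**Working it through.** **Inputs.** Three arms at 1:1:1 (Trial design); blocks of six, hence two families per arm, within two counties (Randomisation); 60 families (Sample size considerations); about 20 families a month (Recruitment). The article gives no predictability figure to reproduce.

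**Ceiling: all earlier allocations in the county are known.** A block is one of 6!/(2!·2!·2!) = 90 equally likely orderings. Before each position:

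| Position | Assignment certain | At least one arm excluded | Best guess correct |
|---|---|---|---|
| 1 | 0 | 0 | 1/3 |
| 2 | 0 | 0 | 2/5 |
| 3 | 0 | 1/5 | 1/2 |
| 4 | 0 | 3/5 | 8/15 |
| 5 | 1/5 | 1 | 3/5 |
| 6 | 1 | 1 | 1 |
| Sum | 1.2 | 2.8 | 3.367 |
| Share of 6 | 20.0% | 46.7% | 56.1% |

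For example, before position 4 no arm is excluded only if the first three families all went to different arms, which has probability (4/5)(2/4) = 2/5. The chance of an exclusion is therefore 3/5. The 47% includes the 20%.

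For 60 families in complete blocks this gives 0.20 × 60 = 12 certain and 0.467 × 60 = 28 with an arm excluded. If incomplete last blocks are allowed, over county splits from 10/50 to 50/10, the ranges are 10.8 to 12.0 and 25.6 to 28.0.

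**With families pending.** Suppose k same-county families are ahead in the queue and not yet allocated. The observer then sees k fewer positions, so each column shifts down by k rows:

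- k = 1: certain 0.2/6 = 3.3%; arm excluded (1/5 + 3/5 + 1)/6 = 30%.
- k = 2: certain 0; arm excluded (1/5 + 3/5)/6 = 13.3%.
- k = 3: certain 0; arm excluded (1/5)/6 = 3.3%.

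Pending families are likely. Baseline outcomes precede randomisation, and the primary measure is a 7-day wear, which implies roughly a week between visit and allocation. If the counties recruit equally (an assumption), each takes in about 10 families a month, or 10/4.35 ≈ 2.3 a week.

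**Could 8-week visits reveal the open block?** At 10 families a month per county, a block of six fills in 0.6 months, about 2.6 weeks. An 8-week visit reveals an allocation made about 7 to 8 weeks earlier, in a block already closed. The block would still be open only if the county recruited fewer than about 6/(8/4.35) ≈ 3.3 to 6/(7/4.35) ≈ 3.7 families a month.

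**Varying blocks.** These were simulated with 30 families per county, sizes equally likely, and an observer who knows the set of sizes and all earlier allocations but not the order of the sizes:

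| Block sizes | Certain | Arm excluded | Best guess correct |
|---|---|---|---|
| 6 only (exact) | 20.0% | 46.7% | 56.1% |
| 6 and 9 | 4.8% | 13.3% | 53.4% |
| 6, 9 and 12 | 2.3% | 6.6% | 51.9% |

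**The case against.** The strongest reply is that 20% and 47% describe an ideal observer whom the article does not place in a position to act. The coordinator looks up arms after baseline and is nowhere said to book, recruit or measure families; data collection belongs to two trained research staff. Families refer themselves and eligibility is broad, so there is little room to steer. Fixed blocks of six with independent list generation are conventional, and a journal article may omit how roles were divided or whether the block size was withheld. Varying the blocks also barely changes best-guess accuracy.

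Most of this stands as a limit on size. It does not remove the weakness. The block size is stated as a design choice, the coordinator sees allocations in order, and the text does not separate that role from the team that books appointments. The benefit of varying blocks lies in certainty and exclusion, the most usable forms of foreknowledge.

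A reader might infer three stronger points that the article does not support:

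- **Visiting staff could predict allocations**, because 8-week visits to early families overlap with later baseline visits. The overlap is real, but at the planned rate those visits reveal blocks that have already closed.
- **The retention criterion is at risk.** It is 75% of index children overall, so moving families between arms has little effect on it.
- **Fixed blocks undermine the masking of research assistants.** Any such unmasking would come from families talking, which varying blocks would not change.

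**Conclusion.** The point holds as a minor allocation-concealment weakness. It is not a contradiction in the plan. At most 20% of assignments could be known and at most 47% narrowed, and only by someone who knows the block size and every earlier allocation in that county, with nobody pending. At the stage of booking, one or two pending same-county families reduce this to about 3% and 30%, or to 0% and 13%. It would therefore be too strong to say that 1 in 5 assignments can be known when families are booked or measured.

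Any effect would run through booking order or conversion effort to the arm contrasts and FRESH-arm adherence. No size of bias can be derived from the article, and the pilot states that it will not support conclusions of effectiveness. The conclusion assumes that the coordinator, or someone told past allocations, knows the block size and has some influence on recruitment; the article neither confirms nor excludes this.

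**What to change.** In Randomisation, replace the fixed block of six with randomly varying block sizes that are multiples of three (for example 6 and 9), generated within county by the independent statistician. State that the sizes are not disclosed to the coordinator or to staff who recruit or measure families. Avoid a fixed block of three, which is more predictable (33% certain, 67% with an arm excluded).

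The gain, when no family is pending, is a fall in certain predictions from 20% to about 5% and in arm exclusions from 47% to about 13%. Best-guess accuracy falls only from 56% to about 53%. With families pending, the starting figures are already lower, so there is less to gain.

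The cost is one change to the list-generation code and one sentence in the text. An incomplete last block could leave two arms in a county differing by up to 3 families (4 if blocks of 12 are used) instead of 2.

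Outcome evaluation measures dates baseline to spring/summer 2018. If allocation is already complete, adopt this for the definitive trial and report for the pilot who knew the block size and whether the coordinator took part in recruitment.

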### Intervention protocol for FRESH arm families

The development, feasibility, acceptability and refinements made to the intervention prior to the current pilot trial have been previously described.^21^ In brief, the intervention the FRESH arm will receive is primarily a goal-setting and self-monitoring intervention, delivered online, aimed at increasing PA in whole families. The intervention uses concepts from the socio-ecological model^32^ and family systems theory^33^ and operationalises constructs from self-determination theory^34^ to inform behaviour change strategies. A detailed description of the FRESH intervention components, behaviour change techniques, targeted theoretical constructs and hypothesised mediators is in table 1. Additionally, the FRESH logic model can be found in figure 3.

**Figure 3 F3:**
[figure not shown]
FRESH theoretical model. FRESH, Families Reporting Every Step to Health.

**Table 1 T1:** Summary of FRESH pilot trial intervention components*

Intervention components	Dose	Description	Behaviour change techniques	Targeted SDT constructs	Hypothesised mediators
1. ‘Family time’	Minimum 1×/week, 10–20 min	‘Family time’ is expected to provide a weekly (at minimum) opportunity for index children† and family members to review, revise and update their family action planners. Family action planners prompt families to plan PA, monitor weekly steps, and discuss any potential upcoming PA barriers and strategies to overcome them. Index children will be allocated as their family’s ‘team captain(s)’ leading in challenge selection and uploading steps on the FRESH website.	Goal-setting Self-monitoring Positive feedback on progress Social support Praise Positive reinforcement	Perceived competence Perceived relatedness Perceived autonomy	Social support Family social norms for PA PA awareness Basic needs satisfaction PA motivation
2. FRESH website	Minimum 1×/week, 5–20 min	The FRESH website will provide a place for families to self-monitor their step counts and set goals by selecting challenges of varying difficulty. Specifically, the website allows families to ‘walk’ around the world by choosing one of three target cities to ‘walk to’ weekly. The challenges are framed as an easy, moderate or hard challenge, which represents a 0%, 5% or 10% increase, respectively, relative to the average steps they take in preceding weeks. Once adults and children accumulate an average of 10 000 and 12 000 steps/day, the step challenge increases will be reduced to 0%, 2.5% and 5%, respectively. Families will also have access to: A general resources area with suggestions for activities that families could do together. A map for a visual representation showing the locations families have travelled to. A step calculator that will convert activities not captured by pedometers to steps (eg, swimming). Their families’ **step history** by challenge. A **leaderboard**. Families will opt in to being included in a leaderboard that is updated weekly, where families get points for: selecting a challenge; uploading steps; completing a challenge; accumulating a family average of 10 000 steps/day over the week; increasing steps from the previous week and going on streaks (eg, five completed challenges in a row). Families with an ongoing challenge will receive **email reminders** to log steps 3 days and 1 day before an impending challenge ends.	Goal-setting Self-monitoring Positive feedback on progress Rewards	Perceived competence Perceived relatedness Perceived autonomy	Social support Family social norms for PA PA awareness Basic needs satisfaction PA motivation
3. Pedometry	Throughout intervention (8 weeks)	All family members will receive pedometers to enable self-monitoring and provide immediate feedback. To allow families to view their progress towards their proximal and distal step goals, they will be encouraged to log their steps onto the FRESH website and/or onto the family action planners.	Self-monitoring Immediate feedback	Perceived competence Perceived autonomy	Social support Family social norms for PA PA awareness Basic needs satisfaction PA motivation
4. Competence reinforcement/rewards	~1×/week (8 weeks)	After completing a challenge or if the challenge week ended, to praise effort (ie, competence reinforcement), children received **personalised supportive letters in the mail** and messages on the FRESH website. They also received small online and **tangible rewards**. Online rewards will include virtual passport stamps (ie, virtual rewards) and access to reinforcement materials (ie, interactive information about the cities they have walked past during their challenge). **Tangible rewards** will be in the form of collectable FRESH cards, which display the city names corresponding with the families’ challenge. The cards will also enable family to play a card game version of ‘rock, paper, scissors’. Children will receive two to four passport stamps/cards for completed challenges (ie, as difficulty increased, more stamps were awarded) and one passport stamp/card for an incomplete challenge.	Feedback on progress Rewards	Perceived competence	Basic needs satisfaction PA awareness

*This table has been adapted from our feasibility study^21^; bolded text indicates new elements added for the FRESH pilot trial (ie, postfeasibility study).

†The index child refers to the child aged 7–11 years in the family.

FRESH, Families Reporting Every Step to Health; PA, physical activity; SDT, self-determination theory.

A week after baseline measures, each family allocated to the FRESH arm will have an hour-long kick-off meeting, scheduled in the family home (or an alternative location can be arranged) with a facilitator. The facilitator will introduce families to the intervention components, accompanying materials (eg, family action planner) and distribute pedometers. Families will also receive their first of four pieces of generic walking information (described in protocol for pedometer-only families section below). However, the main goals of this meeting are to familiarise families with the intervention website and their pedometers and to prompt weekly ‘family time’ meetings (described in table 1) in which they complete their action planners and select a new challenge city to ‘walk to’ on the FRESH intervention website. All families will receive a follow-up phone call a week after their kick-off meeting to discuss any issues or ask any clarifying questions. Participant-initiated distant support will continue to be available, where participants can contact the research team with questions or to report issues (eg, website bugs and pedometer issues).

Table 1 provides a detailed description of the FRESH intervention components. In each family, the index child (or children, if multiple) will be designated the role of ‘team captain(s)’, which involves taking the lead in selecting challenges and uploading steps online. Evidence suggests that children may act as change agents to elicit changes to the psychosocial environment^14^; therefore, promoting the index children to the role of family ‘team captain(s)’ may strengthen child buy-in, perceived autonomy and improve intervention fidelity. All family members will be given pedometers, wearing them for as long as possible daily, to capture their steps during challenges. Pedometers are simple to use, convenient, and are associated with effective interventions for increasing parent-child PA^35^. After the challenge week is over, whether a family completes their challenge or not, they will receive personalised competence reinforcement messages praising their effort online and hardcopy letters (addressed and mailed to all participating children in the family). In addition, online and tangible rewards will be given to participating children after a challenge week. If a family does not complete a challenge, they will progress to a hidden city along their challenge route, as opposed to the city they chose, and will still receive a reinforcement message and reward, as described. Families with an ongoing challenge will receive email reminders to log steps 3 days and 1 day before an impending challenge ends. After every challenge week, the described cycle will repeat starting with the next ‘family time’ meeting. Following assessments at 8 weeks postbaseline, families retain access to the website and their pedometers, and can continue using it for as long as they like. There will also be continued support in terms of website updates (eg, leaderboard and parental resource updates) and participants will continue to receive competence reinforcement letters and rewards.

